### Randomization and blinding

The participants will be assigned to either the UC-MSCs treatment group or the control group in a 1:1 ratio using a block randomization method. A randomization list has been pre-generated. The participants will be blinded to the treatment group throughout the study (Fig. 2).

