### Endpoints

#### Primary endpoints

The primary endpoints of this study include DGF during one week post transplantation, and biopsy proven acute rejection (BPAR) over one year.

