### Study design

This is a prospective multicenter controlled study including three kidney transplant institutions (the third affiliated hospital of Sun Yat-sen University, Zhujiang hospital of Southern Medical University, and the second affiliated hospital of Guangzhou Traditional Chinese Medicine University). The protocol has been approved by the Ethics Committee of Human Study at the three institutions, which were established according to the Operational Guidelines for Ethics Committees that Review Biomedical Research developed by the World Health Organization (WHO) [22].

No organs from executed prisoners will be used in the study, and procurement of kidneys from all donors will be conducted in accordance with the WHO principles, Declaration of Helsinki and Istanbul declaration [23, 24]. Organ donation and recovery will be conducted by organ procurement organizations in the three kidney transplant institutions, which were established by the National Health and Family Planning Commission of China. Before procurement, written consent will be obtained from the donor’s immediate family, agreeing to donation of the kidney and withdrawal of life support. The obtained consent for donation will be then reported to the Organ Donation Committee, which supervises the donation process.

All the participants in this study will provide informed, written consent to undergo this study. Participants receiving renal transplantation with deceased-donor grafts will be recruited and randomly divided into two groups. The trial group will undergo peripheral vein injection of human UC-MSCs in the 48 hours before the operation, and renal arterial injection during the operation. The control group will not receive UC-MSC treatment. All the participants will have standard induction therapy. All the participants will be recruited from the three transplant units and meet the eligible criteria. The Standard Protocol Items: Recommendations for Interventional Trials (SPIRIT) Figure is provided in Fig. 1.

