### Treatment methods

#### UC-MSC treatment

A target of 2 × 10^6^ UC-MSCs per kilogram body weight will be injected via the peripheral vein during the 48 hours before renal transplantation. The dose of UC-MSCs administered via the renal artery during the implantation surgical procedure is 5 × 10^6^ cells.

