DGF is defined as urine output < 1000 ml/day in first 48 hours or failure of serum creatinine to decrease by 10% in the first 48 hours postoperatively, according to Shoskes [26]. BPAR is classified according to the Banff 2013 classification [27]. Renal color ultrasound will be performed at 1 day, 7 days, 1 month, 3 months, 6 months, and 1 year postoperatively. Time-zero biopsy and protocol biopsies at 14 days and 12 months postoperatively will be performed. When acute rejection is suspected clinically, renal allograft biopsy will also be carried out. The incidence of BPAR at 2 weeks, 1 month, 3 months, 6 months, and 1 year after the operation will be recorded. For opportunistic infection, the incidence of CMV, EBV, and BK-viremia will be measured in blood samples, and pulmonary and urinary tract infection will be monitored at 3 months, 6 months, and 1 year after the operation.

Additionally, laboratory examinations such as routine blood and urine tests, tests of liver and renal function, and concentration of CNI will be assessed once a week in the 3 months after the operation, once every 2 weeks in months 3 to 6, and once a month in months 6 to 12.

Adverse side effects in the UC-MSC treatment group may include fever, uncommon arrhythmia and allergic reaction. Adverse events will be recorded and treated. The trial blood samples will be collected to examine safety.

We will make every effort to minimize missing data. Trial enrollment and follow-up procedures will be reviewed during bi-monthly conference calls. We will report rates of missing data for each outcome by study arm and send missing data reports to the sites.

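### Participant blinding cannot hold as described, because only the trial arm has a pre-operative injection; separately, for-cause biopsies leave the BPAR endpoint open to ascertainment that differs by arm

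*Protocol article*

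**What the plan says.** Randomization and blinding makes one masking claim: "The participants will be blinded to the treatment group throughout the study". It names no other role as blinded, whether surgeon, treating clinician, biopsy decision-maker or pathologist.

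Study design describes the arms. For the active arm: "The trial group will undergo peripheral vein injection of human UC-MSCs in the 48 hours before the operation, and renal arterial injection during the operation". For controls: "The control group will not receive UC-MSC treatment". For both: "All the participants will have standard induction therapy". The section UC-MSC treatment repeats the timing of the first injection, which "will be injected via the peripheral vein during the 48 hours before renal transplantation".

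Primary endpoints lists "DGF during one week post transplantation, and biopsy proven acute rejection (BPAR) over one year". Data collection and postoperative monitoring schedules a time-zero biopsy and protocol biopsies at 14 days and 12 months for all recipients, and adds: "When acute rejection is suspected clinically, renal allograft biopsy will also be carried out". BPAR is to be recorded at 2 weeks, 1, 3 and 6 months and 1 year, and graded by Banff 2013.

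**The concern.** Two separate things are at stake.

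The first is accuracy. The article asserts a property of the trial that its own account of the two arms does not support. A reader of the results would credit the trial with participant masking that, on the published description, it does not have.

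The second is how one of the two primary endpoints is ascertained. Part of the BPAR count depends on someone suspecting rejection and ordering a biopsy, and no masking is claimed for the people who do so. If that threshold differs between arms, the observed BPAR rates can differ with no difference in rejection. This route runs mainly through clinicians. Participants' reporting of symptoms is a secondary route. Repairing or deleting the blinding sentence would therefore not close it.

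**Working it through.** **Blinding statement against the treatment descriptions**

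| Element | UC-MSC arm | Control arm | Visible to the participant? |
|---|---|---|---|
| Peripheral-vein injection, within 48 h before surgery | Yes | None described | Likely, since it precedes the operation |
| Renal arterial injection during surgery | Yes | None described | Could go unnoticed |
| Standard induction (ATG, methylprednisolone, then prednisone, MMF, CNI) | Yes | Yes | Same in both arms |

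The only element that could conceal the pre-operative injection would be a matching injection in controls. None appears in the Abstract, Study design, UC-MSC treatment or Standard induction therapy. A consented participant could infer the allocation from whether that injection was given. The reactions listed for the UC-MSC group (fever, arrhythmia, allergic reaction) could be a further clue.

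**Where BPAR can be detected**

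- Day 14: protocol biopsy, regardless of suspicion.
- After day 14 and before 12 months: for-cause biopsy only. Any new case counted at 1, 3 or 6 months comes from here.
- 12 months: protocol biopsy. It may not show an episode that was treated without biopsy and has resolved.

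The sample size rests on 6-month acute rejection, so the planning figure covers an interval in which, after day 14, only for-cause biopsies can find cases.

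**Illustration of size**

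The plan gives no figure to reproduce. Inputs:

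- p = 16.7%, the control-group acute rejection rate in Sample size. It is a 6-month figure from the earlier study, used here for both arms (no true effect).
- n = 50 per arm, from Sample size.
- s = share of BPAR found only by for-cause biopsy. Assumed 25%, 50%, 75%.
- r = relative reduction in those biopsies in the UC-MSC arm. Assumed 10%, 25%, 50%.

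Observed UC-MSC rate: p₂ = p × (1 − s × r). Spurious difference: d = p − p₂.

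Chance of a two-sided 5% result favouring UC-MSC (normal approximation): Φ[(d − 1.96 × SE₀)/SE₁], with SE₀ pooled and SE₁ unpooled. The nominal value in that direction is 2.5%.

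| s | r | p₂ | d (points) | Chance of a false result favouring UC-MSC |
|---|---|---|---|---|
| 25% | 10% | 16.3% | 0.4 | 3% |
| 25% | 25% | 15.7% | 1.0 | 3% |
| 25% | 50% | 14.6% | 2.1 | 5% |
| 50% | 10% | 15.9% | 0.8 | 3% |
| 50% | 25% | 14.6% | 2.1 | 5% |
| 50% | 50% | 12.5% | 4.2 | 9% |
| 75% | 10% | 15.4% | 1.3 | 4% |
| 75% | 25% | 13.6% | 3.1 | 6% |
| 75% | 50% | 10.4% | 6.3 | 15% |

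Last row in full:

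- p₂ = 0.167 × (1 − 0.75 × 0.50) = 0.1044, so d = 0.0626.
- Mean rate 0.1357, so SE₀ = √(2 × 0.1357 × 0.8643/50) = 0.0685.
- SE₁ = √[(0.167 × 0.833 + 0.1044 × 0.8956)/50] = 0.0682.
- (0.0626 − 1.96 × 0.0685)/0.0682 = −1.05, and Φ(−1.05) = 0.147.

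In patients, the range is 0.004 × 50 = 0.2 to 0.063 × 50 ≈ 3.1 per arm. If the reduction fell on the control arm instead, the same differences would appear with the sign reversed. With about 8 events per arm (0.167 × 50 = 8.4), the normal approximation is rough.

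**The case against.** The strongest reply is that silence is not a statement. The sentence on controls rules out UC-MSCs but not a vehicle injection. The blinding section points to Fig. 2, which is not available here, and a condensed article may leave the mechanics of masking to the full protocol. This stands as far as it goes: the conclusion is that blinding cannot hold as described, not that no sham was used. It does not dispose of the point, because what controls receive is core content that the article does describe, and that description conflicts with an affirmative claim.

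The second reply is that the bias route does not follow from the blinding sentence. That is right. The sentence covers participants, while the biopsy decision lies mainly with clinicians, for whom no blinding is claimed. The two points are therefore kept separate.

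The third reply is that safeguards exist: protocol biopsies in all recipients at 14 days and 12 months, and Banff grading. They limit the problem but leave the interval between them uncovered. The other primary endpoint, DGF, rests on urine output and creatinine in the first 48 hours and is little affected.

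A reader might infer more: that participants are awake and know their arm, that surgeons and clinicians know it, that the trial is in fact open-label, or that fewer biopsies in the UC-MSC arm would produce a favourable BPAR result. The documents state none of these. Clinicians watching a new cell product could equally biopsy more often, which would push the difference the other way.

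**Conclusion.** The contradiction holds on the text and depends on no calculation: participant blinding throughout is claimed, and the arms as described do not allow it. The one condition is that a matching injection, if used, is not reported in the article.

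The ascertainment point is a vulnerability, not a demonstrated bias. It rests on BPAR between day 14 and 12 months being detectable only by for-cause biopsy, and on masking being claimed for no one who orders or reads biopsies. Its direction and size are not fixed by the documents. Under the assumed shares and reductions, the spurious difference is 0.4 to 6.3 percentage points, with a 3% to 15% chance of a false result in one direction against a nominal 2.5%. That spans negligible to material. The correction should be made, but the point does not by itself invalidate the BPAR comparison.

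**What to change.** 1. Reconcile the Randomization and blinding section with Study design and UC-MSC treatment. Either state the masking procedure actually used, including any vehicle or sham injection in controls, or withdraw the blinding claim and describe the trial as open-label. State also who else, if anyone, is blinded.
2. Have the existing pathologists read biopsies under a study code with arm information removed. This addresses bias in reading only, not in the decision to biopsy. Trial status says recruitment continues, so it can still be applied to the remaining biopsies.
3. Report the number of for-cause biopsies by arm, so that any difference in biopsy frequency is visible.
4. Add a supportive BPAR analysis limited to the 14-day and 12-month protocol biopsies. Acknowledge that it misses rejection diagnosed and treated between them and so measures a different outcome from the primary one.

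The cost is a weaker masking claim, coded labels on biopsies already planned, one table of counts and one extra analysis. No treatment, visit or sample size changes.

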**Fig. 2 Fig2:**
[figure not shown]
Overview of this trial procedure UC-MSCs, umbilical-cord-derived mesenchymal stem cells

### Data collection and postoperative monitoring

Baseline clinical demographics of donors (such as age, gender, body mass index, medical history, infection status, serum creatinine, causes of death, time of ICU, urine volume per day, creatinine level at organ procurement, time of warm and cold ischemia, use of vasoactive drugs and cardiopulmonary resuscitation) will be documented. For recipients, clinical data include age, gender, medical history, current medication, blood type, previous blood transfusions, PRA, infection status, physical examination, laboratory examinations, methods of dialysis, and duration of dialysis. HLA mismatching numbers of donor-recipient, complement-dependent cytotoxicity (CDC), time-zero donor kidney biopsy will also be collected. All immunosuppressive and other drugs used and dosages administered will be recorded during the study. Follow up will be in accordance with the assessment schedule in Table 1.

**Table 1 Tab1:** Assessment schedule for recipients

Procedure	Time point											
	BL	Tx	POD1	POD2	POW1	POW2	POW3	POW4	POW12	POW24	POW36	POW48
Medical history	×											
Transplantation information		×										
Concomitant medication	×	×			×	×	×	×	×	×	×	×
Physical examination	×		×	×	×	×	×	×	×	×	×	×
Blood sample test	×		×	×	×	×	×	×	×	×	×	×
Urinalysis	×		×	×	×	×	×	×	×	×	×	×
Viral load CMV and BK virus									×	×		×
Urine volume			×	×	×	×	×	×	×	×	×	×
Renal color ultrasound			×		×				×	×		×
Time-zero and protocol biopsies		×				×						×
CNI concentration					×	×	×	×	×	×	×	×
Safety assessment	×	×	×		×	×	×	×	×	×		×
Infection assessment									×	×		×
Chest CT scan	×								×	×		×

*BL* baseline, *Tx* renal transplantation, *POD* post operation day, *POW* post operation week, *CMV* cytomegalovirus, *CNI* calcineurin inhibitor, *CT* computed tomography

DGF is defined as urine output < 1000 ml/day in first 48 hours or failure of serum creatinine to decrease by 10% in the first 48 hours postoperatively, according to Shoskes [26]. BPAR is classified according to the Banff 2013 classification [27]. Renal color ultrasound will be performed at 1 day, 7 days, 1 month, 3 months, 6 months, and 1 year postoperatively. Time-zero biopsy and protocol biopsies at 14 days and 12 months postoperatively will be performed. When acute rejection is suspected clinically, renal allograft biopsy will also be carried out. The incidence of BPAR at 2 weeks, 1 month, 3 months, 6 months, and 1 year after the operation will be recorded. For opportunistic infection, the incidence of CMV, EBV, and BK-viremia will be measured in blood samples, and pulmonary and urinary tract infection will be monitored at 3 months, 6 months, and 1 year after the operation.

Additionally, laboratory examinations such as routine blood and urine tests, tests of liver and renal function, and concentration of CNI will be assessed once a week in the 3 months after the operation, once every 2 weeks in months 3 to 6, and once a month in months 6 to 12.

Adverse side effects in the UC-MSC treatment group may include fever, uncommon arrhythmia and allergic reaction. Adverse events will be recorded and treated. The trial blood samples will be collected to examine safety.

We will make every effort to minimize missing data. Trial enrollment and follow-up procedures will be reviewed during bi-monthly conference calls. We will report rates of missing data for each outcome by study arm and send missing data reports to the sites.

### Sample size

The sample size was calculated based on our previous data showing that there was no BPAR in the MSC treatment group at 6 months after transplantation, compared with 16.7% of acute rejection in the control group [21]. Based on this preliminary study, we calculated that 44 patients per arm will be required to achieve power of 90% with a two-sided significance level of *P* < 0.05. To account for possible dropouts (10%), the target number of patients was, therefore, set at 50 per arm (100 in total) (see Additional file 1).

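### The 90% power figure is built on 6-month rejection rates with exactly 0% in the UC-MSC arm, and is not supported for the primary endpoint of BPAR over one year

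*Protocol article*

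**What the plan says.** The Primary endpoints section of the protocol article names two primary endpoints: DGF in the first week and "biopsy proven acute rejection (BPAR) over one year".

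The Sample size section plans on rejection only. It cites the group's previous study, where "there was no BPAR in the MSC treatment group at 6 months after transplantation, compared with 16.7% of acute rejection in the control group". From these rates it states that "44 patients per arm will be required to achieve power of 90" per cent at a two-sided 0.05 level, and it raises the target to 50 per arm for 10% dropout. It gives no 12-month rate, no assumption linking 6 to 12 months, and no reason for the shorter horizon.

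The Data collection and postoperative monitoring section states: "Time-zero biopsy and protocol biopsies at 14 days and 12 months postoperatively will be performed". Table 1 places the last of these biopsies in post-operative week 48. The same section records BPAR incidence at 6 months and at 1 year as separate time points, so the protocol itself treats them as different quantities.

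**The concern.** The planning contrast stops at 6 months, while the endpoint runs to 12 months and takes in one more scheduled biopsy. Both additions can only add BPAR events to an arm; they cannot remove any.

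This matters most in the UC-MSC arm. Its planning rate is zero, the lowest value possible, so the one-year rate can only equal or exceed it. With so few events expected, power is very sensitive to the first few in that arm.

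A reader who takes the 90% as the chance of detecting the effect on one-year BPAR could read a null result as stronger evidence against benefit than the design allows.

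**Working it through.** **Inputs.** Control rate 16.7%, UC-MSC rate 0%, two-sided alpha 0.05, 44 per arm before and 50 per arm after dropout (all from Sample size); 1:1 allocation (Randomization and blinding). The article gives no 12-month rates, so every rate below other than 0% and 16.7% is an assumption.

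**Formula (pooled normal approximation).** With p̄ = (p1 + p2)/2,

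power = Φ{ [ |p1 − p2|·√n − 1.96·√(2p̄(1 − p̄)) ] / √(p1(1 − p1) + p2(1 − p2)) }

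**Step 1. The plan's own case: 16.7% against 0%, n = 44.** p̄ = 0.0835.

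(0.167·√44 − 1.96·√(2·0.0835·0.9165)) / √(0.167·0.833) = (1.108 − 0.767)/0.373 = 0.914, so power is 82%.

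The result depends on the test. Exact power at 44 per arm is 95% for the uncorrected Pearson test and 77% for Fisher's test. The pooled formula needs 56 per arm for 90%. The failure of 44 to reproduce is a separate point. For the present one, changes must be read within one method, not against the stated 90%. The dropout step is consistent: 44/0.9 = 48.9, rounded up to 49, against 50 planned.

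**Step 2. Same added late risk r in both arms.** For patients free of BPAR at 6 months, the 12-month rates become 0.167 + 0.833r (control) and r (UC-MSC).

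Example, r = 5%: control 0.167 + 0.833·0.05 = 0.209, UC-MSC 0.05, difference 0.159, p̄ = 0.129. At n = 44: (1.052 − 0.930)/0.461 = 0.265, so power is 60%.

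| Late risk r | Control vs UC-MSC | Pooled, 44 per arm | Pooled, 50 per arm |
|---|---|---|---|
| 2% | 18.4% vs 2% | 73% | 78% |
| 5% | 20.9% vs 5% | 60% | 66% |
| 10% | 25.0% vs 10% | 46% | 51% |

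Against the 82% of step 1, the losses at 44 per arm are about 9, 22 and 36 percentage points.

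**Step 3. Only the UC-MSC rate moves; control fixed at 16.7%.**

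| UC-MSC rate | Pooled, 44 per arm | Pooled, 50 per arm |
|---|---|---|
| 0% | 82% | 87% |
| 2% | 66% | 72% |
| 4% | 50% | 55% |
| 5% | 42% | 47% |

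This is the harsher scenario, because late risk and the 12-month biopsy apply to controls as well. The sensitivity does not come from the approximation: exact Pearson power at 44 per arm, with control 16.7%, is 95%, 76% and 46% at UC-MSC rates of 0%, 2% and 5%.

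**Step 4. Only the control rate moves; UC-MSC fixed at 0%.** Pooled power at 44 per arm is 82% at control 16.7%, 89% at 20% and 96% at 25%. A large enough rise in controls can also offset a small rise in the UC-MSC arm: 25% against 2% gives 90%.

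**The case against.** The strongest reply is that a longer horizon need not cost power. Cumulative incidence cannot fall, so if 16.7% is right at 6 months it is a floor for controls at one year, and step 4 shows power rising with the control rate. This stands. A reader might infer that the trial is underpowered for one-year BPAR, or that every planning value is the most favourable possible. The documents support neither reading: the second is true of the 0% alone, and the first would need 12-month rates that the article does not give.

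A reader might also add the 82% of step 1, or the Bonferroni correction in Statistical analysis, to the size of this point. Both are separate matters, and neither arises from the horizon or from the zero rate.

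The biopsy argument is softer than it looks. BPAR is classified by Banff 2013, but the article does not say outright that rejection seen only on a protocol biopsy counts, nor whether the earlier study took protocol biopsies. There is also a protocol biopsy at 14 days, so detection of this kind is not confined to the second half of the year. The six extra months of risk remain either way.

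Finally, the calculation is referred to Additional file 1, which is not at hand, and the Discussion concedes possible lack of power. The additional file could explain the arithmetic, but the Sample size section itself names the 6-month data as the basis. The Discussion gives no figure, mentions neither the horizon nor the zero rate, and leaves the 90% unqualified.

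**Conclusion.** The point holds in this form: the 90% power is stated for a 6-month contrast with a zero rate in the UC-MSC arm, and the article does not support it for BPAR over one year. The net direction of the error is uncertain.

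The size depends on what is assumed. At 44 per arm with the pooled formula, power runs from 96% (25% against 0%) down to 46% (the same 10% late risk in both arms) or 42% (16.7% against 5%). The decisive assumption is the UC-MSC rate. A one-year rate of 2% with controls unchanged costs about 16 points by the pooled formula (82% to 66%) and 19 by the exact Pearson test (95% to 76%). Enrolling 50 per arm with no dropout does not restore 90% in any scenario of step 2 or step 3.

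**What to change.** Rewrite the Sample size paragraph for 12-month BPAR:

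- State an assumed 12-month rate for each arm, with a UC-MSC rate above zero, and say how each follows from the 6-month data.
- Name the test on which the power is computed.
- Show the resulting power as a range, labelled separately for 44 evaluable and 50 enrolled per arm.
- Withdraw the single 90% figure.

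This costs wording only: no extra patients, procedures or endpoints. A new 6-month secondary endpoint is not needed, because BPAR incidence at 6 months is already recorded. The drawback is that the stated power becomes less favourable. The reproduction of 44 per arm and the Bonferroni level should be settled as separate points.

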Based on the above described mechanism of MSCs on tissue repair, anti-inflammatory and immune mediation, our hypothesis is that human UC-MSCs can prevent DGF in the early post-transplant phase. Moreover, we expect human UC-MSCs to ameliorate IRI and suppress immune response to decrease acute rejection of the graft, thereby avoiding chronic graft dysfunction. Limitations of our study include: (1) this is the first study on application of human UC-MSCs to prevent both DGF and acute rejection of deceased donor kidneys rather than living-related grafts, and the safety and efficacy of human UC-MSCs needs to be monitored; (2) although we identified a significant effect of human UC-MSCs on reduction of both antibody-mediated rejection and AKI in our previous study [21], we may have been underpowered to detect any significant differences in outcomes in this prospective multicenter controlled study.

Taken together, a positive outcome from allogeneic MSCs in terms of preserving renal function to decrease DGF, reducing acute rejection, and prolonging long-term survival will implicate a major advancement for deceased-donor renal transplantation.

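### The 44 per arm stated for 90% power (0% vs 16.7%, two-sided 0.05) is not reproduced by the standard two-proportion formulas, and no test is named that would support it

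*Protocol article*

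**What the plan says.** The Sample size section of the protocol article rests on the group's earlier study. In it "there was no BPAR in the MSC treatment group at 6 months after transplantation", "compared with 16.7% of acute rejection in the control group". From these two rates the article concludes that "44 patients per arm will be required to achieve power of 90% with a two-sided significance level" of 0.05, and raises 44 to 50 per arm (100 in total) for 10% dropout. No test or formula is named, and the reader is referred to Additional file 1, which is not at hand. The Randomization and blinding section fixes allocation "in a 1:1 ratio using a block randomization method".

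Three other places bear on the figure:

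- The Primary endpoints section lists two primary endpoints, delayed graft function and BPAR. Only BPAR is used for sizing.
- The Statistical analysis section plans a logistic model for binary endpoints and a Bonferroni correction.
- The Discussion lists as a limitation that "we may have been underpowered to detect any significant differences in outcomes in this prospective multicenter controlled study".

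**The concern.** Every input to the calculation is printed, so the result can be checked from the article alone. The usual two-sided calculation on those inputs needs about a quarter more patients than stated (56 / 44 = 1.27).

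This is the trial's only quantitative justification of its size. A reader of a null BPAR result would assume a 10% chance of having missed the planned effect. Under the pooled formula that chance is 18%, and under Fisher's test 23%. If the number came from a one-sided level or from 80% power, the printed description of the design is wrong on that input.

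**Working it through.** **Inputs.** Rates p1 = 0.167 (control) and p2 = 0 (cells), two-sided alpha 0.05 and power 90%, all from Sample size. Allocation 1:1, from Randomization and blinding. Difference d = 0.167; mean rate 0.0835.

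**Building blocks.**
- Null term A = √(2 × 0.0835 × 0.9165) = 0.3912
- Alternative term B = √(0.167 × 0.833 + 0) = 0.3730
- z for two-sided 0.05 = 1.960; z for 90% power = 1.2816

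**Attempt to reproduce 44 (two-sided 0.05, 90% power).**
- Pooled: n = [(1.960 × 0.3912 + 1.2816 × 0.3730) / 0.167]² = 55.6, so 56
- Unpooled: n = [(1.960 + 1.2816) × 0.3730 / 0.167]² = 52.4, so 53
- Pooled variance in both terms: n = [(1.960 + 1.2816) × 0.3912 / 0.167]² = 57.7, so 58
- Pooled with continuity correction: 67
- Arcsine: 30 uncorrected, 54 corrected
- Fisher's exact test by enumeration: 54

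None gives 44. Reading 16.7% as exactly 1/6 leaves 56, 53 and 58 unchanged.

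**Power at the stated sizes.**
- Pooled at 44: Φ[(0.167 × √44 − 1.960 × 0.3912) / 0.3730] = Φ(0.914) = 82.0%
- Unpooled at 44: Φ[0.167 × √44 / 0.3730 − 1.960] = Φ(1.010) = 84.4%
- The same two formulas at 50: 86.7% and 88.6%

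**Exact power.** With a true rate of 0% in one arm, that arm always has no events. Power is then the probability that the control arm reaches the smallest count x that the test rejects against 0.

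| Test (two-sided 0.05) | Rejects from | Power at 44 | Power at 50 | n per arm for 90% |
|---|---|---|---|---|
| Fisher | 6 vs 0 | 76.6% | 86.3% | 54 |
| Boschloo | 5 vs 0 | 88.0% | 93.6% | 46 |
| Barnard (pooled z) | 4 vs 0 | 95.0% | 97.6% | 39 |
| Pearson, uncorrected | 4 vs 0 | 95.0% | 97.6% | 39 |

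At 44 per arm, Barnard's p-value for 4 vs 0 is 0.042, so it holds its level. Pearson's true type I error at a common rate of 8.35% is 6.0% at 44 per arm and 4.8% at 50. The likelihood-ratio test has 98.5% power at 44 but a type I error of 6.9%, and it would need only 31.

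**Where 44 does fit.**
- One-sided 0.05 with 90% power: 45.1, so 46 (pooled), or 42.7, so 43 (unpooled). Pooled power at 44 is 89.3%.
- Two-sided 0.05 with 80% power: 41.9, so 42 (pooled), or 43.1, so 44 (pooled variance in both terms).

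**Dropout step.** 44 / 0.9 = 48.9, so 49. Rounding up to 50 is sound.

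**With Bonferroni.** If alpha is split over the two primary endpoints (0.025 each, z = 2.241), pooled power at 44 is Φ[(0.167 × √44 − 2.241 × 0.3912) / 0.3730] = Φ(0.619) = 73%, and 66 per arm would be needed for 90%.

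**The case against.** The strongest counter-argument is that the normal approximation is poor when one arm is at 0%, so 82% is not the power of any particular test. Barnard's test is valid at two-sided 0.05 and has 95% power at 44. Pearson's test, which the pooled formula approximates, also reaches 95%, and at 50 per arm its error at the planning rate is below 5%. This stands. A reader might infer that 44 per arm cannot give 90% power under any valid test, or that the true chance of missing the effect is about double the stated 10%. The documents support neither as a general statement. That chance at 44 is about 5% (Barnard, Pearson), 12% (Boschloo), 18% (pooled formula) or 23% (Fisher).

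This does not rescue the printed sentence, which says that 44 are required. Barnard and Pearson require 39 and Boschloo 46, and the article names none of them. The analysis it does name, a multi-level logistic model, gives no ready support either: with no events in one arm the ordinary odds ratio has no finite estimate.

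Additional file 1 may show the method. It cannot change the inputs printed in the article. If it used a one-sided level, the printed sidedness is the error.

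A reader might also take the limitation in the Discussion as an admission that the 90% is wrong. It is a general caution about outcomes, gives no figure, and mentions neither 44 nor 90%.

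**Conclusion.** The point holds in this form: 44 per arm for 90% power at two-sided 0.05 is not reproduced from the article's own inputs by the standard formulas (53 to 58 per arm, or 67 with continuity correction) or by Fisher's test (54). Under the pooled, unpooled and Fisher calculations, power at 44 is 82%, 84% and 77%. The dropout margin does not restore 90% even if nobody drops out, since at 50 per arm these methods give 87%, 89% and 86%.

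The size of the shortfall depends on the test. Under Boschloo it is small, and under Barnard or Pearson there is none, although 44 is still not the number these tests require. That a one-sided level or 80% power lies behind 44 is plausible from the arithmetic but cannot be established from the article. All figures take the planning rates of 0% and 16.7% as given. Apart from the 73%, they use an unadjusted 0.05.

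**What to change.** In the Sample size section, name the test, the formula, the sidedness and the alpha behind the calculation, including whether alpha is divided between the two primary endpoints. Replace the 90% claim with the power that this method gives at 44 and at 50 per arm. At two-sided 0.05 that would be, for example, about 82% and 87% by the pooled formula, or 77% and 86% by Fisher's test. If a one-sided level was used, correct the two-sided statement. If alpha is split, quote the power at the split level (about 73% at 44 by the pooled formula).

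The change is to wording only, and enrolment stays at 50 per arm. The cost is that, by these methods, the stated power becomes less favourable.
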